### Aim 3: To establish proof-of-concept and test Hoosier Sport Re-Social's feasibility, acceptability, and appropriateness

#### Aim 3: design

The third phase of the study will evaluate the feasibility of the Hoosier Sport Re-Social intervention (#NCT06556719) with 6th through 9th grade students from a rural middle or high school, conducted twice weekly over an 8-week period (ORBIT Phase Ib). Our assessment will focus on recommended feasibility measures for feasibility studies [28]. Alongside these measures, we will explore outcomes including self-reported weekly moderate-to-vigorous physical activity (MVPA) and physical literacy, body satisfaction, daily social media use duration, various psychosocial factors (such as self-esteem, body appreciation), and psychological needs using the BPNSFS.

Following the initial feasibility test, we will refine and retest the *Hoosier Sport Re-Social* intervention during the subsequent semester. To support intervention delivery, college student mentors—enrolled in upper division undergraduate or graduate public health programs—will collaborate with our research team. These mentors will undergo a 4-week training course before working with the middle or high school students. Their participation in delivering the intervention will be part of their academic coursework, earning them credit hours. The intervention is delivered by trained college students enrolled in upper-division public health and kinesiology courses. This model supports sustainability and scalability by leveraging an existing service-learning partnership between the university and the rural school. It also enhances relatability, as adolescents may feel more comfortable engaging with near-peer facilitators.

Our hypotheses for Aim 3 include several expectations: achieving full enrollment *(N* = 50), retaining 85% of participants by the intervention’s end, maintaining a 75% attendance rate, obtaining a mean score of ≥ 16 (considered a “good” score) on the Feasibility of Intervention Measure (FIM), AIM, and IAM, and ensuring an 80% fidelity rate in adhering to intervention procedures. Our selection of implementation measures (AIM, FIM, IAM) aligns with core constructs from the Theoretical Framework of Acceptability (TFA) and maps onto RE-AIM dimensions (e.g., implementation and acceptability). This approach supports a structured evaluation of the intervention’s feasibility and future scalability. The Hoosier Sport Re-Social intervention is described in accordance with the Template for Intervention Description and Replication (TIDieR) framework to enhance reproducibility. A structured fidelity checklist has also been developed to monitor delivery, adherence, and adaptations across implementation sessions, ensuring consistency with the intended intervention protocol. Progression to a full-scale randomized controlled trial (RCT) will be considered if the pilot study demonstrates the following: enrollment reaches at least 80% of the target sample (*N* = 50); retention at post-intervention assessment is 85% or higher; session attendance averages 75% or above; fidelity to the intervention protocol is maintained at or above 80% based on fidelity monitoring; and participants report mean scores of at least 16 out of 20 on validated measures of feasibility (FIM), acceptability (AIM), and appropriateness (IAM). These criteria align with recommendations for determining readiness to advance from a pilot to a full-scale trial in behavioral intervention research.

#### Aim 3: setting and sample

For the pilot study, we aim to recruit a total of *N* = 50 6th through 9th grade students. Similar to Aim 2, we will employ convenience sampling, striving for diversity in terms of biological sex and physical activity involvement. Our goal is to enroll an approximate 50% female and 50% male participant ratio, encompassing both regular and non-regular physical activity participants.

To be eligible for participation, students must meet specific criteria: currently enrolled in 6th through 9th grade at the school, possess parental consent to participate, provide their agreement to study participation (assent), commit to attending all school days during the intervention period, and be available for both baseline and post-intervention data collection. These criteria are crucial for the study’s integrity and aim to ensure comprehensive data collection and participation continuity.

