## Methods/design

### Overview

This study is structured into three distinct phases to address body image perceptions and develop interventions for adolescent females enrolled in under-resourced rural middle and high schools (grades 6–9). The first phase, AIM 1, involves conducting a comprehensive needs assessment through community-engaged research to build foundational knowledge about body image, social media usage, and physical activity levels among rural adolescents. This phase aims to identify current physical activity levels and assess facilitators and barriers to positive body image within the adolescents’ context.

In the second phase, AIM 2, the focus shifts to co-designing the Hoosier Sport Re-Social intervention with key community stakeholders. This involves collaborating with adolescents, parents, and teachers to develop a prototype multi-level intervention and implementation protocol. Participant involvement is central to the Hoosier Sport Re-Social protocol. Adolescents, parents, and teachers are not only research participants but also co-creators of the intervention. Through a series of structured co-design sessions, these stakeholders actively contribute to identifying problems, generating solutions, and refining the final prototype, ensuring the program is contextually relevant and responsive to community needs. The goal is to create an intervention that is responsive to the needs and preferences of adolescents, specifically targeting the promotion of a positive body image.

The third phase, AIM 3, involves piloting the Hoosier Sport Re-Social intervention with a sample of 50 adolescents, divided into 25 in the intervention group and 25 in the control group. This phase will evaluate the feasibility and acceptability of the intervention, assessing both trial-related and intervention-specific feasibility indicators. Feasibility refers to the extent to which an intervention can be successfully delivered in a specific setting, considering factors such as recruitment, retention, acceptability, adherence, and implementation fidelity. The overarching hypothesis of the study is that the successful completion of these three phases will result in a feasible and effective intervention protocol for promoting a positive body image among adolescent females in rural settings. Figure 2 provides a timeline of these aims.

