#### Aim 2: setting and sample

We plan to form two co-designer groups, one comprised of parents and the other children, with each group consisting of *n* = 5 recommended group size for participatory design [63]. This odd number of participants allows for a majority vote to resolve ties between design alternatives within the group. Recruitment of adults and children will occur through parent/guardian meetings and school administrators’ weekly newsletters. While utilizing convenience sampling due to limited sample size and time constraints, efforts will be made to enroll an approximately equal distribution of 50% female and 50% male participants, including those regularly involved in social media and those who are not. To be eligible for participation, children must be enrolled in middle or high school, entering 6th to 9th grade, and have parental consent while committing to attend all 5 co-design sessions. Adults eligible for inclusion must be a parent/guardian of a current 6th through 9th-grade student at the school and be willing to attend all 5 co-design sessions.

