#### Aim 2: procedure

The two design teams will engage in a series of five co-design sessions spread across 3 months, with approximately 2 weeks between sessions. The adolescent group will initiate the process, while in parallel, the adult group will alternate sessions with the adolescent group (e.g., adolescent session, adult session, and so forth). The adult group will collaborate with the study team to review and refine the prototype developed by the children, aiming to retain as many adolescent-derived components as possible. This simultaneous yet alternating co-design approach empowers adolescents to incorporate essential concepts such as fun and enjoyment, while allowing adults to refine the intervention protocol for feasibility and practicality. Please see Fig. 4 for additional details.

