#### Aim 2: data analysis

The study will use inductive thematic analysis to analyze qualitative data from semi-structured interviews, aiming to gain insights directly from participants. This analysis involves identifying emerging patterns and themes without imposing predefined categories. Interviews will be transcribed verbatim, followed by an iterative coding process to identify meaningful units and group them into preliminary themes. Themes will be refined through team discussions to ensure accuracy and reliability. Inter-coder reliability will be established by multiple researchers coding a subset of interviews. The final thematic framework will offer a nuanced understanding of participants’ perspectives, informing recommendations crucial for the project’s outcomes. This analysis will serve as a robust basis for evidence-based conclusions and guide the project's direction.

Additionally, we will utilize descriptive statistics to analyze quantitative data derived from the Feasibility of Intervention Measure (FIM), Acceptability of Intervention Measure (AIM), and Intervention Appropriateness Measure (IAM) employed in session 5. To ensure a thorough assessment, we will establish clear criteria for evaluating the success of each feasibility aspect (a mean score of ≥ 16/20). Specifically, for the FIM, success will be determined by meeting a predefined threshold of participant engagement and adherence rates. For the AIM, we will gauge success based on whether participant satisfaction scores meet or exceed established benchmarks, indicating the intervention’s acceptability. The IAM will be evaluated by determining if the majority of participants consider the intervention appropriate based on predefined indicators of suitability and relevance. By the conclusion of session 5’s analysis, we will have a comprehensive draft of the intervention protocol prepared for piloting and feasibility testing in Aim 3. This draft will be informed by the results and success metrics from these measures, ensuring that the protocol is both feasible and well-received.

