##### Acceptability, appropriateness, and feasibility

Adolescents who participate in *Hoosier Sport Re-Social* will rate the feasibility, acceptability, and appropriateness of the intervention using the FIM, AIM, and IAM, respectively (each described in Aim 2).

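### Aim 3 eligibility lets Aim 2 adolescent co-designers into the pilot, and their ratings of their own programme would count toward the FIM, AIM and IAM progression thresholds

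*Protocol article*

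**What the plan says.** All references are to the protocol article.

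- **Who designs the programme.** The Overview states: "Adolescents, parents, and teachers are not only research participants but also co-creators of the intervention". Under Aim 2: setting and sample, "children must be enrolled in middle or high school, entering 6th to 9th grade, and have parental consent", and they commit to all five sessions. The adult criterion ties Aim 2 to the partner school: "Adults eligible for inclusion must be a parent/guardian of a current 6th through 9th-grade student at the school". Under Aim 2: procedure, the adults refine the adolescents' prototype, "aiming to retain as many adolescent-derived components as possible".
- **How many.** Aim 2: setting and sample says "We plan to form two co-designer groups, one comprised of parents and the other children", with five members in each.
- **What the co-designers rate in Aim 2.** In the last session the teams score the prototype on the FIM, AIM and IAM. Aim 2: data analysis says "we will establish clear criteria for evaluating the success of each feasibility aspect (a mean score of ≥ 16/20").
- **Who enters Aim 3.** Students must be "currently enrolled in 6th through 9th grade at the school, possess parental consent to participate, provide their agreement to study participation (assent"), commit to attending, and be available at baseline and post-intervention. Sampling is by convenience, as in Aim 2. Having been a co-designer is not mentioned.
- **Who rates in Aim 3, and to what end.** "Adolescents who participate in *Hoosier Sport Re-Social* will rate the feasibility, acceptability, and appropriateness of the intervention using the FIM, AIM, and IAM". Aim 3: design makes a mean of 16/20 or more on each scale a condition for considering a full-scale trial, alongside enrolment, retention, attendance and fidelity criteria.

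**The concern.** The three scales are in the progression rule to show whether the programme suits rural adolescents in general, most of whom had no hand in making it. A co-designer's view of a programme built largely from the adolescents' own ideas is not that of a newcomer. The Aim 2 and Aim 3 criteria cover the same grades, and both aims refer to the partner school and use convenience sampling, so a co-designer who is still in grade 6–9 meets the Aim 3 criteria as written.

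With about 25 raters, a handful of favourable authors could lift a mean that sits just under 16 to just over it, and a full trial could be considered on that basis. Because the article sets out the eligibility list and the progression rule explicitly, this is a rule it fixes too loosely rather than a detail left to another document.

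**Working it through.** **The plan's own figure.** The only Aim 3 precision figure is ±10% for 85% retention with 50 participants. It reproduces: 1.96 × √(0.85 × 0.15 / 50) = 0.099. This point does not dispute it.

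**Inputs from the article**
- Raters: n = 25. The Overview gives 25 intervention and 25 control, and those who receive the programme do the rating.
- Adolescent co-designers: at most 5 (Aim 2: setting and sample).
- Threshold: mean of 16 on each scale.

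**Assumptions (not in the article)**
- Co-designers score s = 19 to 20.
- The number among the raters is k = 0, 2–3 or 5. If all five enrol and the groups are equal, two or three would be expected in the intervention group. Five is the extreme.

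**Mean needed from the other raters**

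Total needed = 16 × 25 = 400, so required mean = (400 − k·s) / (25 − k).

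| k | s = 19 | s = 20 |
|---|---|---|
| 0 | 16.00 | 16.00 |
| 2 | 362/23 = 15.74 | 360/23 = 15.65 |
| 3 | 343/22 = 15.59 | 340/22 = 15.45 |
| 5 | 305/20 = 15.25 | 300/20 = 15.00 |

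If instead all 50 participants rated and all five co-designers were among them, the others would need (800 − 95)/45 = 15.67 or (800 − 100)/45 = 15.56.

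**What this does to a borderline decision.** Suppose the non-designers' true mean is 15.5, the SD is 3 and co-designers score 3 points higher on average (all assumed). The standard error is 3/√25 = 0.6 and the expected overall mean is 15.5 + 3k/25. The normal approximation gives the chance of passing one scale:
- k = 0: mean 15.50, z = 0.83, chance 0.20
- k = 2: mean 15.74, z = 0.43, chance 0.33
- k = 3: mean 15.86, z = 0.23, chance 0.41
- k = 5: mean 16.10, z = −0.17, chance 0.57

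For SDs from 2 to 4, the k = 0 chance runs from 0.11 to 0.27 and the k = 5 chance from 0.55 to 0.60.

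**The other criteria**
- Retention: 85% of 50 is 42.5, so 43 children. If all five co-designers stay, the others need 38/45 = 84.4%, which is practically unchanged.
- Attendance, extreme case: if five of 25 attend every session, the others need (0.75 × 25 − 5)/20 = 68.75% for the group to average 75%.

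**The case against.** The strongest reply is that nothing in the article plans for co-designers to enrol. It concerns at most five children, and a condensed article may omit how they are handled. The first two parts stand: overlap is only possible, and its size is unknown. It also requires the pilot to include the co-design school, and the site is described differently in the Abstract (two schools), Aim 3: design (a middle or high school) and Aim 3: setting and sample (the school). Co-designers who have passed grade 9 drop out. The third part is weaker, because the article lists its criteria explicitly and has no such restriction.

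It is also fair to say that neither the direction nor the size of an authorship effect is documented, that scores of 19–20 are an assumption, and that high ratings alone cannot produce progression, since enrolment, retention, attendance and fidelity must also pass.

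Several stronger readings are tempting but not supported:
- A reader might infer that Aim 2 ratings must reach 16 before Aim 3 can start, so that the pilot merely repeats a test already passed. Aim 2: data analysis sets 16/20 as a success criterion that informs the draft and states no gate. It applies to whole teams, adults included, and to a prototype rather than a delivered programme.
- A reader might infer that retention is inflated too. The arithmetic shows a negligible effect. For attendance, delivery within physical education and health classes and the attendance commitment required of every participant leave less room for an authorship effect than the extreme case suggests.
- A reader might take Aim 2: design to mean two teams with five adolescents each. Aim 2: setting and sample, procedure and sample size calculation all describe a single adolescent group of five, so the larger number should not be relied on.
- That co-designers are the keenest or easiest children to recruit is nowhere stated.

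**Conclusion.** The point holds in a limited form. The eligibility rule admits Aim 2 co-designers, and nothing in the progression rule separates their ratings from those of other participants.

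The likely size is modest: with two or three co-designers among the raters, the mean required of the others falls by about a quarter to half a point. One point is the extreme, with all five in the intervention group and all scoring 20. This could change the decision only if the non-designers' mean is close to 16. The result rests on 25 raters, assumed co-designer scores of 19–20, and a pilot that includes the co-design school. It is worth correcting because three progression criteria depend on these few ratings and the correction is cheap.

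**What to change.** Co-designers need not be barred from the programme. Add to Aim 3: setting and sample that Aim 2 co-designers may take part and are flagged at enrolment. Add to the progression criteria in Aim 3: design that the FIM, AIM and IAM thresholds are judged on participants who were not co-designers, with co-designers' scores reported separately. Attendance may be shown with and without them. Retention needs no change.

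The flag should be a variable in the de-identified data set, because Aim 3: procedure removes identifiers before analysis.

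The cost is two sentences, one variable and at most about five fewer raters. Going from 25 to 20 widens a confidence interval for a mean score by a factor of about √(25/20) = 1.12, or 12%. If no co-designer enrols, the change costs nothing.

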#### Aim 3: procedure

The initial study recruitment details will be disseminated through email and newsletters by the research team. Adults interested in having their adolescent(s) participate will receive a Qualtrics survey link containing comprehensive study information. Eligibility confirmation will be communicated via email or phone. Upon receiving parental consent, a list of eligible adolescents will be generated for subsequent assent approaches. While risks are minimal, all physical activity sessions will be led by trained staff following school safety procedures. Any injuries or distress will be addressed immediately, with referrals made to school counselors if needed. Adverse events will be documented and reported to the IRB in accordance with institutional guidelines. All participant data will be de-identified and stored on password-protected, encrypted servers approved by the university. Only authorized research personnel will have access to identifiable information, which will be stored separately from survey or outcome data. Hard copy materials will be secured in locked cabinets. Identifiers will be removed from data prior to analysis and publication to ensure confidentiality.

A study information and recruitment session will be organized by the research team at the school site for adolescent participants. During this session, 6th–9th grade students will receive study information and an assent survey using Qualtrics. They will be encouraged to ask questions and informed of their right to discontinue participation at any time during the study. This session ensures that children are well-informed and comfortable with the study details before deciding to participate.

#### Aim 3: measures

Aligned with recently published feasibility research [28], we plan to evaluate two categories of feasibility measures: trial-related and intervention-related indicators. Our trial-related feasibility assessment will encompass gauging our capability for recruitment and retention. On the other hand, our intervention-related feasibility evaluation will involve measuring treatment fidelity, ensuring accurate, consistent, and high-quality delivery of intervention components. We will also assess the acceptability of the intervention, attendance rates, compliance (for instance, using weekly screen time report), cost considerations, and appropriateness, which involves evaluating setting, cultural norms, or specific requirements. These measures will be collected at two distinct intervals: mid-intervention and post-intervention—using Qualtrics recorded through mobile devices. This comprehensive evaluation framework will enable us to thoroughly assess both trial-related and intervention-related feasibility aspects of our study. Please see Fig. 5 for more details.

**Fig. 5 Fig5:**
[figure not shown]
Intervention- and trial-related outcomes

Additionally, preliminary behavior outcomes will be measured through replicating the measures of AIM 1 (BSQ, BAS-2, CAPL-2, pedometer wear, and a youth survey). These combined measures will provide data on potential changes from pre- to post-intervention in body satisfaction, body appreciation, physical literacy and activity levels, and social media usage.

##### Recruitment capability

Recruitment capability will be determined based on the number of children successfully enrolled into *Hoosier Sport Re-Social* (consent from parent/guardian and assent from child).

##### Retention

Retention will be measured based on the number of children who participate in the post-intervention data collection event. A make-up post-intervention event will be scheduled for child participants who miss the post-intervention data collection event.

##### Treatment fidelity

The evaluation of treatment fidelity in our study involves two primary stakeholders: the children participating in the intervention and the research team. Using self-report measures at both mid- and post-intervention points, we aim to understand how accurately, consistently, and effectively the intervention was delivered. This assessment process is guided by three key questions derived from prior research on school-based physical activity implementation [66]: first, *to what extent was the intervention delivered as planned?* Second, *how did the college student mentors adjust the program, if at all?* And third, *what were the underlying reasons for any adaptations made to the intervention?* By involving both the adolescents and the research team in this evaluation, we seek to gain comprehensive insights into the fidelity of the intervention delivery and any modifications made during its implementation.

